## Abstract

**Background:**

Obesity is one of the most prevalent health problems in western societies. However, it seems not effectively managed in the healthcare system at present. Originating from smoking cessation a tool called the 5As for obesity management has been drafted and adapted by the Canadian Obesity Network (CON) to improve weight counseling and provider-patient-interaction. This paper describes the rationale and design of the INTERACT study. The objective of the INTERACT study is to evaluate the effectiveness and intervention costs of a 5As eLearning program for obesity management aimed specifically at general practitioners (GPs).

**Methods:**

The INTERACT study is a cluster randomized controlled trial aimed at implementing and evaluating an online-tutorial for obesity management based on the 5As approach in cooperating primary health care practices. Effectiveness of the 5As intervention will be evaluated by assessing patients and doctors perspectives on obesity management in primary care before and after the training. GPs in the intervention group will get access to the 5As obesity management online-tutorial while GPs in the control group will be assigned to a waiting list. Outcome measures for patients and GPs will be compared between the intervention group (treatment as usual + training of the GP) and the control group (treatment as usual). Hierarchical regression models will be used to analyze effects over time pre- and post-intervention.

**Discussion:**

The 5As present physicians with a simple mnemonic for patient counseling in the primary care context. While the use of the 5As in weight counseling seems to be associated with improved doctor-patient interaction and motivation to lose weight, intervention studies assessing the effectiveness of a short 5A eLearning tutorial for physicians on secondary outcomes, such as weight development, are lacking.

**Trial registration:**

The study has been registered at the German Clinical Trials Register (DRKS00009241; date of registration: 03.02.2016).

## Background

Obesity, defined by a body mass index (BMI) greater than 30 kg/m^2^, is highly prevalent in western countries. According to the World Health Organization (WHO), the worldwide prevalence of obesity has more than doubled within the last 30 years [1]. In Germany, a national survey revealed that 23% of all men and 24% of all women are obese [2]. The consequences of obesity are manifold ranging from severe somatic diseases (e.g. type 2 diabetes, obstructive sleep apnea, cardiovascular disease) and psychiatric co-morbidities [3] to psychosocial impairment in form of stigmatization and discrimination [4–6]. Obesity prevention and treatment have therefore been put on the agendas of the WHO [7].

Primary care physicians have a crucial role when designing weight management programs as they see their patients on a regular basis and over a long period of time [8]. Additionally, studies showed that patients who wish to reduce weight based on their doctor’s advice reduce more weight and can be motivated more by their general practitioner (GP) [9, 10]. However, patients themselves are not likely to address obesity and weight reduction with their GP and may not even consider their GP as ideal person to support them in weight management goals [11]. In fact, patients may even perceive their attending GPs to be responsible for initiating the discussion about weight and weight management [12]. Studies in the German health care system indicate that weight management in primary care is unsatisfactory in several aspects. Aside from being under-recognized [8], obesity in primary care patients is often not addressed by the physicians [13]. Other research showed that conservational strategies are seen most effective and therefore recommended far more often by health care professionals [14, 15]. However, even these strategies seem not consistently discussed with patients. Barriers include negative attitudes towards patients with obesity, a lack of knowledge of the overall pathophysiology of obesity and familiarity with current guidelines on the management of obesity, as well as a lack of self-efficacy in weight counseling [15–17].

Originated from smoking cessation counseling, a tool called the 5As (assess risk, ask about readiness to lose weight, advise change, assist in establishing interventions and securing goal attainment and arrange follow up) has been proposed to be adapted and used in weight counseling [18]. In smoking cessation, the use of the 5As has been successfully promoted and tested [19, 20]. A positive impact on quit rates and motivation has been reported after the transfer to the primary care setting [19].

Studies using the 5As in weight loss settings show that their use is positively correlated with patient motivation and intention to lose weight [21]. While some GPs already intuitively rely on components of the 5As in weight counseling, studies analyzing the quality of physician-patient encounters show a lack of consistency and a failure to include all 5As in counseling [22, 23]. The Canadian Obesity Network (CON) has set out to develop a standardized framework for the use of the 5As in weight counseling that combines the Canadian Obesity Guidelines [24] with the structural framework of the 5As and consists of hand-out material and an online tutorial [25]. All components (ask, assess, advise, agree, assist) have been elaborated in detail and provide clear guidance in counseling [26]. A pilot study showed a positive impact on quality of counseling and provider-patient-communication in the short term [27]. Results from long-term studies, however, are lacking.

### Objectives

The objective of the INTERACT study is to evaluate the effectiveness and intervention costs of an online-tutorial implementation for obesity management in primary care. The online-tutorial aims at increasing the quantity and quality of provider-patient interaction regarding weight management in patients with obesity and improving patient motivation and weight management goals. The aim of this study is to evaluate the online-intervention on the quality of the provider-patient-interaction.

## Methods/design

### Study design and study setting

The INTERACT-study comprises a cluster randomized controlled trial (cRCT) to implement and evaluate the effectiveness of an e-learning program (the 5As tutorial) for obesity management aimed specifically at GPs. The trial will be conducted within the primary care setting in the region of central Germany. The Institute of Social Medicine, Occupational Health and Public Health of the University of Leipzig (ISAP) has established a primary care physician network that consists of collaborating GPs. Based on this network, primary care physicians will be contacted and invited to participate in the study. The Interact trial includes patients with obesity recruited from cooperating GPs. Primary efficacy endpoint will be the assessment of the provider-patient interaction regarding obesity and weight management from the patients’ perspective.

### Intervention scheme

For the present study, we have developed a 30 min online-tutorial based on the 5As framework of obesity management by the CON which covers recommendations on how to discuss weight with the patient (ASK), assess obesity related risks and causes of weight gain (ASSESS), advise on treatment options (ADVISE), agree on weight loss expectations and treatment plan (AGREE) and assist the patient in the ongoing process of losing weight (ASISST). The 5As framework has the potential to improve weight management counselling to patients by encouraging GPs to start sensitive conversations with the patient and achieve agreement on weight management goals and strategies. A key principle of the 5As framework is to measure the success of weight management in improvements in overall health and well-being rather than in the amount of weight loss. The 5As online-tutorial includes five knowledge sections that cover the 5As and the current state of knowledge on obesity management. The online-tutorial contains a short knowledge quiz at the end. An overview of the 5As is provided in Fig. 1. The 5As online-tutorial will be implemented in cooperating primary health care practices. Participating GP practices will be randomly allocated either to the intervention group with continuous access to the 5As online tutorial or to the control group, where GPs will be assigned to a waiting list condition. Waiting list practices will gain access to the 5As online-tutorial 6 months after the trial ended. GPs of the intervention group will be sent access data to the 5As online-tutorial after return of the baseline questionnaire (BL) and will have continuous access to the 5As program throughout the trial. Intervention completion by GPs of the intervention group will be checked and GPs will be reminded to complete the 5As intervention within two months after gaining access to the tutorial. CME points (Continuing Medical Education) will be granted after completion of the intervention module. Patients with obesity will be recruited in cooperation with participating GP practices. Patients of both groups (intervention group, control group) will be assessed using comprehensive questionnaires at recruitment (baseline, BL) as well as 6 and 12 months follow-up (after recruitment). GPs of both groups will be asked to complete questionnaires at BL (after recruitment) and 12 months follow-up. Furthermore, GPs of both groups will be asked to assess the health and weight status of each of their recruited patients immediately after patient inclusion and 12 months after patient inclusion. Participating GPs and patients will be invited to complete the follow-up assessments by postal reminder. A flow diagram of the overall intervention scheme is provided in Fig. 2.

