### Randomization and blinding

GPs, who agree to participate, will be sequentially allocated to either the intervention or the control group by a trained staff member at the Institute of Social Medicine, Occupational Health and Public Health (ISAP) external to the project. Randomization will be done by adaptive randomization [28] applying the biased coin method and using a computerized random number generator. Given that the intervention is addressed at the practitioners, it is not possible to blind GPs to their group allocation. However, GPs will be blinded to knowledge of the primary outcome measures. Patients will be blinded with regard to the group allocation. Participating GPs will be informed about allocation to control or intervention group after randomization completion by postal mail including a sealed envelope with the assigned intervention category. They will further be sent recruitment material and consent forms for patients by postal mail. In addition, GPs will receive explanatory instructions about the recruitment material and the recruitment process by telephone through a research assistant who will not be involved with tracking of patient enrollment or data collection. GPs will receive an instruction how to recruit patients in a blinded manner. Practitioners will identify and recruit patients according to the inclusion and exclusion criteria within their practices. They will inform eligible patients about the study and ask them to participate. Information material and consent forms for patients are identical for intervention and control group. The statistician analyzing the data will be unaware of the group allocation. The investigator and the research team will remain blinded to the results until data collection is completed.

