### Outcomes and measures

#### General practitioners

GPs will be asked to complete two short pre- and post-intervention questionnaires. The pre-intervention questionnaire will be filled out upon recruitment (BL). The post-intervention questionnaire will be sent by postal mail 12 months after BL. Pre- and post-intervention questionnaires will contain closed questions on referral and counseling behavior of patients with obesity, satisfaction with own knowledge about obesity, attitudes towards obesity as a chronic disease, relevance of different causes of weight gain and attitudes on different aspects of obesity management. Stigma concerning obesity will be assessed using the Fat Phobia Scale (FPS) by Bacon et al. [29]. The FPS consists of 16 pairs of adjectives on a semantic differential. Furthermore, GPs of the intervention group will be asked to evaluate the 5As online tutorial in regards to the relevance of its knowledge contents and its usability within the primary care setting 12 months after intervention completion.

Furthermore GPs will be provided with a list of co-morbid conditions and will be asked to complete this list and assess the weight status for each participating patient at BL and 12 months follow-up.

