#### Patients

Patients will be asked to complete three questionnaires at recruitment as well as 6 months and 12 months follow-up, respectively. All three questionnaires will be sent by postal mail. In addition to demographics (gender, age, educational level, working status, marital status), the outcome measures for patients will include patient-doctor interaction regarding obesity management over the past 6 months, quality of life, weight history and BMI, motivation to engage in weight management strategies, self-stigma regarding obesity, the assessment of depressive and anxiety symptoms and personality traits. Instruments for each of the mentioned outcomes are described in the subsections below. As the 5As framework primarily aims to improve weight management counselling by improving the interaction between patients with obesity and their physicians the primary outcome of this study will focus on the patient-doctor interaction. Changes in weight will be assessed as a second outcome after investigating improvements in the patient-doctor interaction regarding weight counselling.

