### Data analysis

After completion of the trial data cleaning and quality control will be conducted. Prior to testing the effectiveness of the intervention, appropriate statistical tests will be used to examine possible baseline differences between groups (e.g. age, sex, educational level, employment status and marital status). Hierarchical regression models will be used to analyze treatment effects from baseline to follow up. Models will be adjusted for the baseline outcome value and confounding factors, such as age, sex and socio-economic background. All analyses will be intention-to-treat in order to control for non-random dropout effects. Patterns of missing values will be inspected and, if applicable, replaced using appropriate statistical methods. Additionally, the effect of the intervention on provider knowledge, satisfaction with own knowledge and perceived counseling behavior will be analyzed. The level of statistical significance will be set at *p* < 0.05 for all statistics.

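### Tutorial access is not tied to completion of the patients' baseline questionnaires, so some intervention-arm baseline PACIC scores can follow the GP's training

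*Protocol article*

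**What the plan says.** The protocol article sets out the timing in several places.

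- **Release of the tutorial** (Intervention scheme): "GPs of the intervention group will be sent access data to the 5As online-tutorial after return of the baseline questionnaire (BL". The sentence is about GPs and refers to a single questionnaire without saying who fills it in.
- **GP's own baseline form**: the General practitioners subsection says "The pre-intervention questionnaire will be filled out upon recruitment (BL". The Intervention scheme says "GPs of both groups will be asked to complete questionnaires at BL (after recruitment) and 12 months follow-up".
- **GP's rating of each patient** (Intervention scheme): a further task, in which GPs "assess the health and weight status of each of their recruited patients immediately after patient inclusion".
- **Patients' baseline**: patients "will be assessed using comprehensive questionnaires at recruitment (baseline, BL) as well as 6 and 12 months follow-up (after recruitment". The Patients subsection adds: "All three questionnaires will be sent by postal mail".
- **Order of allocation and patient recruitment** (Randomization and blinding): GPs are told their allocation after randomization. Then, "They will further be sent recruitment material and consent forms for patients by postal mail". They go on to identify and recruit eligible patients themselves.
- **Analysis** (Data analysis): "Models will be adjusted for the baseline outcome value".

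The Abstract (Methods) says that the views of patients and doctors are assessed both before and after the training. The primary outcome, the 5A PACIC sum score, covers the preceding six months (Primary outcomes).

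**The concern.** If the GP's own form releases the tutorial, an intervention GP who returns it promptly can complete a 30-minute course before, or while, recruiting patients. A patient recruited later, or one who fills in the mailed form after seeing the trained GP, then reports a baseline PACIC that includes some trained care. Control GPs have no access, so only one arm is affected.

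A baseline measured after randomization and open to influence by the intervention is no longer a neutral covariate. Adjusting for it subtracts part of the effect the trial is meant to estimate. The bias is towards no difference. The power section treats 15 points as the clinically significant change, so a shrunken estimate also affects how the result is read.

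**Working it through.** **1. The plan's own figure.** Inputs from Power calculation and sample size: difference 15, SD 20, power 95%. Alpha 0.05 is from Data analysis; two-sided is assumed.

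n per group = 2 × (1.960 + 1.645)² × 20² / 15² = 46.2, rounded up to 47. The stated 47 reproduces.

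**2. Order of events as written.** (a) The GP agrees and is randomized. (b) The GP learns the allocation and receives patient recruitment material. (c) The GP recruits patients one by one. (d) Each patient's baseline belongs to that patient's own recruitment and comes by post. (e) Tutorial access follows return of one baseline questionnaire.

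Only the position of (e) is open. If the form is the GP's and is completed when the GP joins, (e) can precede (c) and (d). If it is completed after the GP's patients are recruited, (e) follows (c), but still nothing makes it follow the return of the forms in (d).

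**3. Size of the bias if it occurs.** Let f be the share of the 15-point effect already present, on average, in the intervention arm's baseline, and rho the slope of follow-up on baseline (the correlation, if the SDs are equal). Then

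adjusted effect = 15 − rho × (f × 15) = 15 × (1 − rho × f).

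Neither rho nor f is given in the protocol; the values below are assumptions.

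| rho | f = 0 | f = 0.25 | f = 0.5 |
|---|---|---|---|
| 0.3 | 15 | 13.9 | 12.8 |
| 0.5 | 15 | 13.1 | 11.3 |
| 0.7 | 15 | 12.4 | 9.8 |

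For scale: f = 0.25 arises if half of the intervention patients answer after training and their scores carry half of the effect (0.5 × 0.5).

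A simulated cluster trial (20 GPs, 7 patients each, ICC 0.05, regression of follow-up on arm and baseline) gave, for rho = 0.5, mean estimates of 15.0, 13.1 and 11.3 at f = 0, 0.25 and 0.5. This agrees with the formula.

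**4. Effect on power.** Take the stated 66 per group as it stands, ICC 0.05 and 6.5 patients per practice. The design effect is 1 + 5.5 × 0.05 = 1.275, and the effective n is 66 / 1.275 = 51.8 per group. Power = Φ(d / (SD × √(2/51.8)) − 1.96). With rho = 0.5:

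| | f = 0 | f = 0.25 | f = 0.5 |
|---|---|---|---|
| SD 20 | 96.8% | 91.6% | 81.6% |
| SD 20 × √(1 − 0.5²) = 17.3 | 99.3% | 97.1% | 91.1% |

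The second row lets the baseline reduce the residual variance, as adjustment normally would. On that row, modest contamination costs more in the size of the estimate than in power.

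**The case against.** The strongest reply is that the harmful order is not established. The trigger sentence does not name the respondent. In the Intervention scheme, recruitment otherwise refers to patients, so a GP form completed after recruitment could mean after the GP's patients have been recruited; access would then also follow patient recruitment. The Abstract states a pre-training measurement for patients. Fig. 2, the flow scheme, is not shown in the text at hand and may settle the order. Mailing rules are also the kind of detail that an article leaves to the full protocol.

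Much of this stands. A reader might infer that GPs are trained before patient baselines by design, or that the pre/post comparison is invalid. The documents support neither. Nor do they support the extreme figures that the formula yields at f = 1, namely 7.5 points at rho = 0.5 and 4.5 at rho = 0.7. Those need every intervention baseline to carry the full effect. With a six-month recall, a form completed soon after training still describes mostly untrained care, and reminders allow up to two months for completing the tutorial.

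Two parts of the reply do not stand. Even the protective reading leaves access free to precede the return of mailed patient forms. And this is not a detail left out: the article states a release rule, and the rule as stated does not secure the measurement order that the Abstract promises.

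**Conclusion.** The point holds in a conditional form. As written, release of the tutorial depends on a questionnaire that is most naturally the GP's own, not on completion of the practice's patient baselines. Some intervention-arm baseline PACIC scores can therefore be obtained after training, and adjusting for them would bias the effect towards zero.

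The loss is rho × f × 15 points. Over rho 0.3 to 0.7 and f 0.25 to 0.5, a true 15-point effect would be estimated at between 13.9 and 9.8 points. If all patient baselines precede training, nothing is lost. The range rests entirely on assumed values of rho and f, and the text does not show that f is above zero. The change is worth making because the bias is one-sided, affects the primary outcome and is cheap to prevent.

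**What to change.** - Reconcile the Abstract, the Intervention scheme and the General practitioners subsection: say whose baseline questionnaire triggers access, and whether recruitment there means that of the GP or of the patients.
- Release access to an intervention practice only when the baseline questionnaires of its recruited patients have been returned, or when a fixed closing date for that practice is reached, with patients enrolled before that date. The closing date keeps one non-responder from holding up a practice.
- Keep the 6- and 12-month follow-ups counted from each patient's recruitment. Moving them to a practice date would make the interval between baseline and follow-up vary with recruitment date, and the problem does not require it.
- If access cannot wait, add a sensitivity analysis not adjusted for baseline PACIC, or one that leaves baselines completed after the GP's training out of the adjustment. The second needs the dates of tutorial completion and of each patient's baseline form.

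The cost is one mailing rule. Training would start some weeks later in slowly recruiting practices, so their earliest patients would have slightly less exposure at 6 months.

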
**Fig. 1 Fig1:**
[figure not shown]
Overview of the 5As for obesity management [25]

**Fig. 2 Fig2:**
[figure not shown]
Cluster-randomized trial intervention scheme

### Inclusion/ exclusion criteria

No exclusion or inclusion criteria apply for the GPs. Patients will be recruited if they fall within the BMI and age range (BMI greater than 30 kg/m^2^, age 18 to 60 years) but do not present at the GPs with an acute illness that needs priority management. The criteria for inclusion and exclusion of participants are summarized in Table 1.

**Table 1 Tab1:** Criteria for inclusion and exclusion of participants

Criteria for inclusion:	
- Body mass index greater than 30 kg/m^2^	
- Age between 18 and 60 years	
- German as native language	
Criteria for exclusion:	
- Acute physical or mental illness that needs priority management and make study participation impossible according to the GP	

